## Abstract

**Objective::**

To describe the study protocol and statistical analysis plan that will be used to evaluate whether methylene blue reduces interventions aimed at controlling hypotension during renal replacement therapy as compared to usual care.

**Methods::**

BLUE is a randomized, multicenter, open-label trial. Patients with high risk of hypotension during renal replacement therapy will be randomized to receive either methylene blue infusion at a dose of 1mg/kg as a bolus, followed by continuous infusion of 0.1mg/kg of body weight in a total of 200mL of saline solution throughout the dialysis session, or to usual care. The usual care group will not receive any intervention. A total of 260 patients is expected to be randomized in a 1:1 ratio.

**Results::**

The primary outcome will be a composite of any of the following events: (1) initiation of vasopressor therapy or an increase of at least 20% from baseline dose; (2) interruption of the renal replacement therapy session; or (3) interruption of fluid removal at the request of the attending physician at any point during the session. Secondary outcomes include the occurrence of hypotension during the hemodialysis session, the maximum vasopressor dose within the first 24 hours, intensive care unit mortality, and in-hospital mortality.

**Conclusion::**

The BLUE study will provide evidence on the role of methylene blue in preventing hypotension during renal replacement therapy.

## INTRODUCTION

Renal replacement therapy (RRT) is widely employed in intensive care units (ICUs) for the management of acute or chronic kidney failure.^(1)^ Continuous RRT (CRRT) offers greater hemodynamic stability compared to conventional intermittent hemodialysis, particularly in hemodynamically unstable patients. However, its limited availability, high cost, and the absence of clear evidence of superiority over intermittent RRT regarding mortality or renal recovery hinder its widespread adoption – especially in resource-limited settings.^(2)^ As a result, intermittent RRT remains the most commonly used modality in these environments.

Intradialytic hypotension (IDH) is a frequent complication during intermittent RRT, with an incidence that may reach up to 70% in critically ill patients.^(3)^ Managing IDH poses a significant clinical challenge, as it is associated with increased morbidity and mortality, higher rates of catheter-related thrombosis, reduced likelihood of renal recovery, and impaired fluid and electrolyte control.^(4)^ Additional consequences include premature interruption of fluid removal, volume overload, and diminished dialysis efficiency.^(5)^

During hemodialysis, endothelial nitric oxide synthase activators may be upregulated through mechanisms not yet fully understood. Contact with dialysis membranes promotes cytokine release by monocytes, inducing tissue injury, increasing endothelial nitric oxide synthase activity, and, consequently, greater nitric oxide production.^(6)^ Endothelial nitric oxide plays a key role in cardiovascular regulation, particularly in blood pressure control. Excessive nitric oxide secretion can result in unwarranted vasodilation, leading to hemodynamic instability. The hypotensive effect and direct cytotoxicity of nitric oxide can lead to tissue hypoxia and multi-organ dysfunction.^(7)^

Methylene blue is a synthetic dye that acts as an inhibitor of the nitric oxide production pathway. Unlike conventional vasopressors, its effect occurs by inhibiting the nitric oxide-cGMP cascade, a central mechanism in RRT-related vasoplegia. This unique property supports its investigation as a preventive strategy against intradialytic hypotension or hemodynamic deterioration during hemodialysis sessions. Its main potential application would be as an adjunctive agent, reducing catecholamine requirements in the management of intradialytic hypotension.^(8)^

We hypothesize that methylene blue infusion can reduce the frequency of hypotension during RRT and, consequently, decrease unwarranted interruptions to this therapy. To our knowledge, no randomized clinical studies have used methylene blue during RRT in critically ill patients. To test this hypothesis, we designed this multicenter, randomized clinical trial to evaluate whether methylene blue infusion during RRT sessions, compared with usual care, reduces interventions aimed at controlling IDH.

The primary objective is to describe the study protocol and statistical analysis plan that will be used to evaluate whether methylene blue reduces interventions aimed at controlling hypotension during RRT as compared to usual care. The secondary objectives are to evaluate whether methylene blue reduces the incidence of hypotension, vasopressor dose requirements within the first 24 hours, ICU and in-hospital mortality, and adverse events.

## METHODS

### Study design and participating sites

This is a pragmatic, randomized, multicenter, open-label, controlled clinical trial. Critically ill patients admitted to the ICU who require RRT and who have a high risk of hypotension will be randomly assigned to receive methylene blue or usual care during the RRT session. The study protocol adheres to the SPIRIT 2013^(9)^ reporting guidelines.

The study will be conducted in five ICUs. The coordinating center is the *Hospital São Paulo* ICU at the *Universidade Federal de São Paulo* (UNIFESP). The other centers are general ICUs with a mixed population of clinical and surgical patients. All institutions have RRT management protocols implemented.

### Trial organization and oversight

An independent Data and Safety Monitoring Board (DSMB) will oversee the trial, ensuring safety, conducting an interim analysis, and determining whether to continue the study. The Research and Ethics Committee of the UNIFESP approved this study under the number 4.952.266, followed by approval from the *Hospital do Serviço Social da Indústria do Papel, Papelão e Cortiça do Estado de São Paulo* (SEPACO) Ethical Committee, the Ethics Committees of *Hospital São José*, and the *Hospital das Clínicas* of the *Faculdade de Medicina* of the *Universidade de São Paulo* (USP).

Written informed consent will be obtained from all participants or their legally authorized representatives before inclusion in the trial. The study is registered on the clinicaltrials.gov platform (identifier: NCT05092165) and is funded by a research grant from the *Conselho Nacional de Desenvolvimento Científico e Tecnológico* (CNPq).

### Eligibility criteria

Participants with a clinical indication for intermittent RRT - whether for acute or chronic kidney dysfunction and regardless of whether it is their first hemodialysis session - who are at high risk of developing hypotension will be eligible for inclusion. High risk of intradialytic hypotension is defined as the need for vasopressor support, adjusted at the discretion of the attending physician, or a systolic blood pressure below 100mmHg.^(10)^

Participants will be enrolled after meeting all inclusion criteria and none of the exclusion criteria, as outlined in table 1. Study sites will maintain continuous records of all patients who meet the inclusion criteria but are not enrolled, along with the reasons for non-inclusion, in accordance with the Consolidated Standards of Reporting Trials (CONSORT) guidelines.^(11)^

**Table 1 t1:** Eligibility criteria

Inclusion criteria	Exclusion criteria
Patients over 18 years old Acute kidney injury or acute-on-chronic kidney disease requiring intermittent renal replacement therapy, hemodialysis Systolic blood pressure lower than 100mmHg or use of a vasopressor Signed informed consent	Pregnancy Life expectancy is less than 24 hours Exclusive palliative or end-of-life care Renal replacement therapy due to hypertensive crisis Known allergy to methylene blue Known glucose-6-phosphate dehydrogenase deficiency Prior participation in the study cute coronary syndrome Chronic nitrate oral use

RRT - renal replacement therapy.

### Randomization and allocation concealment

Participants will be randomized to receive either methylene blue or usual care through a centralized, web-based automated randomization system (RedCap® UNIFESP). The randomization list will be generated electronically on random.org by an external individual not involved in the study, using variable block sizes of 4 - 6, stratified by center and prior vasopressor use. Randomization access will be available 24 hours a day, 7 days a week. Each registration number will be randomized only once to prevent the same participant from being randomized more than once in the study. Randomization will be carried out automatically without the investigators’ knowledge. The participating centers were unaware of the block sizes to ensure allocation concealment. The flowchart is available in figure 1.

**Figure 1 f1:**
[figure not shown]
Participants’ allocation.

### Blinding

Blinding of healthcare professionals is not feasible due to methylene blue's distinct visual appearance. However, outcome assessors and statisticians will remain blinded to group allocation to minimize bias.

### Outcomes

The primary outcome will be a composite consisting of any of the following events: (1) initiation of vasopressor therapy or an increase in vasopressor dose by at least 20% from baseline; (2) interruption of the RRT session; (3) interruption of fluid removal at the request of the attending physician at any point during the session. No predefined interruption criteria were established due to the wide range of clinical scenarios encountered in patients undergoing RRT; thus, decisions regarding treatment interruption were left entirely to the attending physician's discretion and will not be adjudicated.

Secondary outcomes include the occurrence of hypotension during the RRT session, the maximum vasopressor dose within the first 24 hours after the hemodialysis session, the cumulative norepinephrine equivalent (NEE) dose,^(15)^ the RRT session fluid balance, the 24-hour fluid balance, ICU mortality, and in-hospital mortality. Hypotension will be defined as a sustained drop in mean arterial pressure (MAP) below 65mmHg. We will assess potential adverse events related to methylene blue use, specifically: acute myocardial infarction, hemolytic anemia, cardiopulmonary arrest during the session, and worsening of gas exchange. We will present all outcome data as specified in table 1S (Supplementary Material). The trial sequence is available in figure 2.

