### Data collection

Demographic characteristics, comorbidities, and severity of illness will be collected at baseline for all participants (Table 2S - Supplementary Material). Renal replacement therapy main characteristics and baseline hemodynamic data will be collected (Table 3S - Supplementary Material), and vital signs will be recorded every 15 minutes by the nursing team via invasive blood pressure or automated non-invasive blood pressure for the duration of the session, along with any changes in vasoactive drug use (Table 4S - Supplementary Material). We will collect variables assessed up to 24 hours, then participants will be followed until hospital discharge to determine survival status or death.

Participants who are withdrawn from the study for safety reasons (excluding those who withdraw consent) will be included in the analysis on an intention-to-treat basis. Any adverse events occurring within the first 24 hours after the hemodialysis session will be documented (Table 5S - Supplementary Material). Adherence to the intervention will also be recorded (Table 6S - Supplementary Material). The data collection schedule is presented in table 7S (Supplementary Material).

Data will be collected via electronic forms using the RedCap platform and securely stored. Forms will be completed by the investigators, who will use specific passwords to access them. Training will be provided for all personnel involved in the study to ensure high-quality data collection. The principal investigator will be available for any questions regarding form completion. Data consistency will be periodically reviewed, and any discrepancies will be addressed by contacting the sites for clarification and correction.

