### Safety and adverse events

Given the severely ill ICU population who regularly undergo hemodialysis, we anticipate potential complications. These events will only be considered adverse events if they are potentially related to the study treatment, are unexpected to the attending physician, and are unrelated to the underlying critical illness that led to RRT.

Serious adverse events will be those that are life-threatening, result in death, lead to prolonged hospitalization, or cause severe and permanent disability. Serious adverse events will be adjudicated by independent physicians and reported to the DSMB and ethics committees. Details on adverse events are available in the notes.

Information on adverse events will be collected. As this involves a critically ill ICU population, various physiological alterations are expected, including laboratory abnormalities and vital sign changes, as well as those resulting from ongoing treatments. Therefore, expected abnormalities will not be considered adverse events unless there is suspicion or confirmation that the event is related to the study intervention.

Adverse events of special interest - those already known to be associated with methylene blue, regardless of severity - will also be recorded. These include hypertension (defined as systolic blood pressure above 180mmHg), chest pain, nausea, vomiting, gastric reflux (defined as reflux greater than 500mL within 6 hours after the start of dialysis), malignant hyperthermia (defined as the occurrence of hyperthermia associated with muscle rigidity, metabolic acidosis, hypercapnia, and/or rhabdomyolysis), hemolytic anemia (defined by the presence of anemia accompanied by clinical signs such as jaundice, together with laboratory evidence of red blood cell destruction such as elevated lactate dehydrogenase - LDH, increased indirect bilirubin, low haptoglobin, and/or reticulocytosis) and worsening of gas exchange, defined as a ≥ 20% decrease in the in partial pressure of oxygen in arterial blood/fraction of inspired oxygen (PaO_2_/FiO_2_) ratio as an absolute increase of 20% in FiO_2_ requirement, if blood gases were not available. In addition, any adverse events deemed by investigators to be possibly related to the study drug must also be documented. These data will be collected only within the first 24 hours following the drug infusion.

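### Adverse-event collection has two conflicting 24-hour origins, one of which controls do not have, and the maximum-vasopressor-dose window, read literally, leaves out the treated session

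*Protocol article*

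**What the plan says.** The protocol article states a 24-hour window in several sections.

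- **Outcomes:** one secondary outcome is "the maximum vasopressor dose within the first 24 hours after the hemodialysis session". The same list has "the RRT session fluid balance, the 24-hour fluid balance", the latter without an origin. Cardiac arrest occurring in the session is named among the adverse events to be assessed.
- **Data collection:** "Any adverse events occurring within the first 24 hours after the hemodialysis session will be documented". The general follow-up sentence reads "We will collect variables assessed up to 24 hours", with no origin.
- **Safety and adverse events:** "These data will be collected only within the first 24 hours following the drug infusion". The same section counts gastric reflux over the six hours from the start of dialysis.
- **Abstract, Results:** "the maximum vasopressor dose within the first 24 hours, intensive care unit mortality, and in-hospital mortality". **Introduction, objectives:** "vasopressor dose requirements within the first 24 hours". Neither names an origin.

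Under Interventions, the bolus comes just before the session and the continuous infusion runs through it. Sessions last 2 to 6 hours, and controls receive no methylene blue. Statistical analysis mentions comparisons of adverse events and limits the modified intention-to-treat set to participants who received RRT.

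**The concern.** Two things look wrong.

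First, the two adverse-event rules differ, and the one in Safety and adverse events is worded restrictively. Staff who follow it have no starting point for a control patient. If controls are then collected on the session clock and treated patients on the infusion clock, event frequencies in the two arms refer to different stretches of time. The session clock, read literally, also opens after the period in which Outcomes expects arrests.

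Second, the maximum vasopressor dose is taken after the session. The hypothesis concerns hypotension during RRT, and the drug is given only around and during it. A peak dose reached in the session and weaned before its end would not count. Session end is also a post-randomisation time. Interruption of the session is a component of the primary outcome, so the treatment itself may move the point at which this clock starts.

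At stake are a between-arm safety comparison and the interpretation of one secondary outcome.

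**Working it through.** **1. Does any stated figure rest on the window?** The only calculated figure is 130 per group (Sample size calculation and interim analysis), from 90% versus 75%, two-sided alpha 0.05 and power 0.90. With unpooled variance:

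n = (1.960 + 1.282)² × (0.90 × 0.10 + 0.75 × 0.25) / 0.15² = 10.51 × 0.2775 / 0.0225 = 129.6, rounded up to 130.

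The plan's figure is reproduced. It concerns the primary composite and contains no 24-hour window, so nothing below changes it.

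**2. The adverse-event rules side by side.**

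| Rule | Treated arm | Control arm | Includes the session? |
|---|---|---|---|
| Data collection: after the session | defined | defined | not if read literally |
| Safety: following the infusion, from its start | defined | no origin | yes |
| Safety: following the infusion, from its end | defined | no origin | no |

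The Safety wording does not say whether the clock runs from the start or the end of the infusion. If from the end, and the infusion runs to session end, the two rules roughly coincide in the treated arm. On either reading the rule has no starting point in controls. No reading makes the two rules agree for both arms.

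The reflux definition brings in a third origin, the start of dialysis. For a 6-hour session, its six hours are over before a literal post-session window opens.

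**3. Window arithmetic.** Put time 0 at session start and let the session last L hours, with L from 2 to 6 (Interventions).

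- Window from session start: 0 to 24.
- Window from session end: L to L + 24.
- Overlap: 24 − L hours.

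| L (h) | Post-session window (h) | Overlap (h) | Share of 24 h | Session hours in the post-session window |
|---|---|---|---|---|
| 2 | 2 to 26 | 22 | 92% | 0 |
| 4 | 4 to 28 | 20 | 83% | 0 |
| 6 | 6 to 30 | 18 | 75% | 0 |

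Most of the 24 hours is common to both windows. The hours that differ are the treated ones.

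**4. Are the data there for the other choice?** A window of 0 to 24 hours lies inside the session plus the 24 hours after it. Data collection records vital signs every 15 minutes during the session, together with changes in vasoactive drugs. Vasopressor data are needed up to 24 hours after the session for the outcome as now defined. The maximum from session start can therefore be derived without new measurements.

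**The case against.** The strongest reply is that this is loose wording with limited reach. The vasopressor window is tied to the session, which both arms undergo and which the analysis set requires. In-session effects are measured elsewhere: by the primary composite, by hypotension during the session and by session fluid balance. A post-session maximum dose can be a deliberate complement. The phrase in Data collection may mark the end of follow-up rather than exclude the session, and the explicit listing of in-session arrest in Outcomes supports that. Figure 2 and Tables 1S, 5S and 7S are not shown and may set out the timing.

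Much of this stands, and it rules out several stronger readings that a reader might infer:

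- That the 24-hour outcomes in general have no origin in controls. This is true only of the infusion-based adverse-event rule.
- That the abstract and objectives contradict Outcomes. They leave the origin out, as condensed text often does.
- That in-session arrests would be lost. Outcomes names them explicitly.
- That the post-session maximum has an expected treatment difference of zero. This requires the effect on dose to end with the session, which the article does not say.
- That the clock can shift by at most 4 hours. The 2-to-6-hour range describes sessions set by clinical need, and an interrupted session could end before 2 hours.

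What the reply does not remove is the conflict between Data collection and Safety and adverse events. Both rules are stated in the article, so it is not a matter of omitted detail, and an unseen table cannot make the two sentences agree. Nor can the difference be explained by type of event. The infusion rule covers events of special interest and any event thought possibly drug-related, while Data collection refers to any adverse event.

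**Conclusion.** The point holds in two parts.

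The adverse-event windows contradict each other, and one cannot be applied in the control arm. The text needs one rule before arms are compared.

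The maximum vasopressor dose, read literally, covers 0 of the 2 to 6 treated hours and starts at a time that interruption can move. Changing the origin from session end to session start replaces 2 to 6 of the 24 hours (8% to 25%). How far this would change the estimated effect cannot be derived from the article, which gives no session lengths by arm and no dose profiles.

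The conclusion rests on the literal wording and on sessions of 2 to 6 hours. It concerns one secondary outcome and safety collection.

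**What to change.** Define time zero once, for both arms, as the start of the RRT session, and use a fixed 24-hour window from it that expressly includes the session.

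- **Adverse events:** apply this window in Data collection and in Safety and adverse events, and make it consistent with the in-session events listed in Outcomes. Because the bolus precedes the session, state also that reactions during it are recorded.
- **Maximum vasopressor dose:** use the same window in Outcomes. If a post-session maximum is intended, keep it as an additional outcome labelled as such.
- **Abstract and objectives:** add the origin so that they match. State it for the 24-hour fluid balance too, unless a supplementary table already does.

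Randomisation is a weaker time zero here. The delay from randomisation to the session is not stated, so a 24-hour window from randomisation might not contain the whole session.

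The cost is mainly a wording change in the protocol and analysis plan, best made before the analysis. The one practical check is whether the adverse-event form captures events during the session, and their times, in both arms.

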**Figure 2 f2:**
[figure not shown]
Study timeline.

### Data collection

Demographic characteristics, comorbidities, and severity of illness will be collected at baseline for all participants (Table 2S - Supplementary Material). Renal replacement therapy main characteristics and baseline hemodynamic data will be collected (Table 3S - Supplementary Material), and vital signs will be recorded every 15 minutes by the nursing team via invasive blood pressure or automated non-invasive blood pressure for the duration of the session, along with any changes in vasoactive drug use (Table 4S - Supplementary Material). We will collect variables assessed up to 24 hours, then participants will be followed until hospital discharge to determine survival status or death.

Participants who are withdrawn from the study for safety reasons (excluding those who withdraw consent) will be included in the analysis on an intention-to-treat basis. Any adverse events occurring within the first 24 hours after the hemodialysis session will be documented (Table 5S - Supplementary Material). Adherence to the intervention will also be recorded (Table 6S - Supplementary Material). The data collection schedule is presented in table 7S (Supplementary Material).

Data will be collected via electronic forms using the RedCap platform and securely stored. Forms will be completed by the investigators, who will use specific passwords to access them. Training will be provided for all personnel involved in the study to ensure high-quality data collection. The principal investigator will be available for any questions regarding form completion. Data consistency will be periodically reviewed, and any discrepancies will be addressed by contacting the sites for clarification and correction.

